## Abstract

**Background:**

Approximately 400,000 people who smoke cigarettes survive Acute Coronary Syndrome (ACS; unstable angina, ST and non-ST elevation myocardial infarction) each year in the US. Continued smoking following ACS is an independent predictor of mortality. Depressed mood post-ACS is also predictive of mortality, and smokers with depressed mood are less likely to abstain from smoking following an ACS. A single, integrated treatment targeting depressed mood and smoking could be effective in reducing post-ACS mortality.

**Method/design:**

The overall aim of the current study is to conduct a fully powered efficacy trial enrolling 324 smokers with ACS and randomizing them to 12 weeks of an integrated smoking cessation and mood management treatment [Behavioral Activation Treatment for Cardiac Smokers (BAT-CS)] or control (smoking cessation and general health education). Both groups will be offered 8 weeks of the nicotine patch if medically cleared. Counseling in both arms will be provided by tobacco treatment specialists. Follow-up assessments will be conducted at end-of-treatment (12-weeks) and 6, 9, and 12 months after hospital discharge. We will track major adverse cardiac events and all-cause mortality for 36 months post-discharge. Primary outcomes are depressed mood and biochemically validated 7-day point prevalence abstinence from smoking over 12 months.

**Discussion:**

Results of this study will inform smoking cessation treatments post-ACS and provide unique data on the impact of depressed mood on success of post-ACS health behavior change attempts.

***Trial registration*:**

ClinicalTrials.gov, NCT03413423. Registered 29 January 2018. https://beta.clinicaltrials.gov/study/NCT03413423.

**Supplementary Information:**

The online version contains supplementary material available at 10.1186/s13722-023-00388-9.

## Background

1.2 million individuals survive acute coronary syndrome (ACS; unstable angina, ST and non-ST elevation myocardial infarction) in the US each year [1]. Cigarette smoking is a major risk factor for ACS and ≈ 400,000 survivors per year were smoking prior to ACS [2, 3]. ACS is a “teachable moment,” in that patients are more receptive to smoking cessation messages, and it provides an opportunity to practice abstinence during hospital stays [4]. Smoking cessation in ACS patients reduces mortality by 36–46% [5, 6].

Depressed mood is a major concern in ACS patients. Clinical depression and sub-clinical depression symptoms are much more common in ACS patients than the general population [7, 8]. Symptoms of depression, even when mild, independently predict post-ACS morbidity and mortality [9, 10], and the American Heart Association now recognizes depression as a major risk factor for poor prognosis following ACS [8].

Smokers are more likely to be depressed at the time of ACS and to experience onset of depression post-ACS than people without a smoking history [11–13]. Smokers with depressed mood are less likely to abstain from smoking following an ACS hospitalization [14]. Further, smoking status partially mediates the relationship between depression and subsequent mortality [15–18], suggesting that depressed mood contributes to mortality both directly *and* through interference with smoking cessation. Although there are counseling treatments that address smoking and depression in isolation in ACS patients, there is no integrated treatment that addresses both simultaneously. This is likely one reason why most ACS patients relapse to smoking within 1 year after ACS hospitalization [19, 20] and why treatments for depression post-ACS have resulted in less than expected improvement in morbidity and mortality rates [21]. A single, integrated treatment that targets both depressed mood and smoking could be highly effective in reducing post-ACS morbidity and mortality.

Behavioral Activation (BA) is a counseling intervention with clearly established efficacy for the treatment and prevention of depression in both psychiatric and medical populations [22–25]. Core BA techniques have been successfully applied as components of larger collaborative care interventions in multiple studies of post-ACS depression treatment [26–29]. BA is easier to train than other empirically-supported counseling treatments and can be delivered with fidelity by bachelor’s level practitioners [30–35] or even family members or peers [35]. BA has also recently shown promise for enhancing smoking cessation outcomes in people with elevated depression symptoms [36, 37].

Our team used a series of semi-structured interviews and test cases to systematically develop an intervention integrating gold standard smoking cessation counseling with existing BA based mood management techniques for post-ACS smokers; Behavioral Activation Treatment for Cardiac Smokers (BAT-CS) [38]. The team then conducted a pilot RCT of BAT-CS (n = 64), which demonstrated that the design proposed below is logistically feasible and highly acceptable, and that BAT-CS shows promise for efficacy on smoking cessation and mood outcomes at 6-month follow-up [38]. It is now necessary to establish the efficacy of BAT-CS in a rigorous, fully powered RCT with longer-term follow up.

A fully powered efficacy trial is underway which will enroll 324 daily smokers with ACS. Patients are randomized to 12 weeks of BAT-CS or a control group where counselors provide the same smoking cessation content plus health education content as a contact control for time spent on BA techniques. Both groups are offered the nicotine patch if medically safe. Follow-up assessments are conducted at end-of-treatment (12-weeks) and 6, 9, and 12 months after hospital discharge. We are tracking the occurrence of major adverse cardiac events and all-cause mortality for 36 months post discharge.

The primary aims and hypotheses of this study are:

### Aim I

Test the efficacy of BAT-CS versus control on depressed mood and smoking cessation. *Hypothesis 1a*: Patients treated with BAT-CS will demonstrate significantly greater improvements in mood and significantly higher rates of biochemically verified 7-day point prevalence abstinence over 12 months than control patients. This trial is powered for hypothesis 1a analyses. *Hypothesis 1b*: Patients treated with BAT-CS will also have higher rates of 30-day point prevalence and continuous abstinence since discharge and longer time to smoking lapse and relapse than control patients.

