**Fig. 2 Fig2:**
[figure not shown]
Design overview

**Table 1 Tab1:** Assessments by time point

	Screen	Baseline 1	Baseline 2	Each session	12 weeks/end-of-treatment	6, 9, 12 months	18, 24, 30, and 36 months
*Screening fully*							
Medical diagnosis, current smoking, and other inclusion/exclusion criteria	X						
Cognitive functioning (MMSE [43])	X						
*Participant characteristics*							
Demographics (age, race, etc.)		X					
Medical and smoking history		X					
Nicotine dependence (FTND [50])		X					
Motivation to quit (contemplation ladder [51])		X	X				
MN withdrawal scale [52]			X				
*Primary outcomes*							
Current smoking/smoking since last contact		X	X	X	X	X	X
Use of other tobacco products		X	X	X	X	X	X
Saliva sample for cotinine testing			X		X	X	
Exhaled breath sample for CO testing			X		X	X	
Depressive symptoms (PHQ-9 [53])		X	X		X	X	X
Depressive symptoms (CESD-10 [66])		X	X		X	X	
*Secondary outcomes*							
Positive and negative affect (PANAS [57])		X	X		X	X	X
Reactive anhedonia (SHAPS [68, 69])		X	X		X	X	
Perceived stress scale (PSS-4 [70])		X			X	X	
Health related quality of life (SF-12 [71])		X			X	X	
Exercise tolerance (DASI [72])		X			X	X	
MACE/mortality					X	X	X
Adverse event monitoring			X	X	X	X	X
*Hypothesized BA mediators*							
Pleasant/valued activities (BADS [76], PES [79, 80])		X			X	X	
*Acceptability*							
Treatment acceptability (CSQ-8 [81])					X		
*Potential confounders*							
Medication adherence questions [88, 89]		X			X	X	
Diet/exercise questions [92]		X			X	X	
Counseling sessions attended				X			
Cardiac rehabilitation attendance					X	X	
Outside of study depression treatment					X	X	
Outside of study smoking cessation treatment					X	X	

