#### Power

The proposed study is fully powered for both Aim I primary outcomes (i.e., biochemically confirmed 7-day point prevalence abstinence and depression symptoms on the PHQ-9 over 12 months post discharge). Based on existing data at the time of study design [36, 38, 86], we expect 7-day point prevalence rates to differ by 8% (29% in control, 37% in BAT-CS) at 12 months, representing an odds ratio of 1.4 at 12 months. We will analyze our data longitudinally (see below), thus we base our sample size on the longitudinal effect across the 4 follow-ups (i.e., end-of-treatment and, 6, 9, and 12 months post discharge). We expect a *longitudinal* odds ratio of 1.33 ending with an 8% between-group difference at 12 months as described above. It is important to note that experts have proposed that increasing rates of smoking cessation in ACS patients by even 5% would have a large impact on public health [87]. Given the assumptions above and an alpha level of 0.05, a total sample size of 324 participants would be required in order to have sufficient (80%) power to test the *longitudinal* effect on intent-to-treat 7-day point prevalence abstinence over 1 year post-discharge. This sample will be more than sufficient (power > 80%) to detect even small longitudinal effects on depression symptoms over 1 year (i.e., with 324 participants we have 80% power to detect between group effect of f squared = 0.03).

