## Discussion

Approximately 400,000 ACS patients who smoke are discharged from the hospital annually in the US [1–3]. Thus, even modest improvements in the rate of smoking cessation post-ACS could save thousands of lives [87]. Moreover, results of this study may also provide insight into the role of smoking in the relationship between depression and cardiac morbidity and mortality in ACS patients and provide a model for how to investigate the role of other health behaviors in this relationship (e.g., diet, physical activity, medication adherence). The work of integrating treatments that can address both psychological distress and health behavior changes into existing medical systems and discovering sustainable models is crucial to long-term intervention impact. If this study shows BAT-CS to be efficacious for smoking, we plan to propose a multi-site effectiveness study focused on integration into ongoing hospital systems, cost-effectiveness, and long-term sustainability.

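### Hypothesis 1a asserts benefit on both mood and abstinence, but the stated power is per outcome: requiring both gives less than 80%, and letting each stand alone at 0.05 gives about 9–10% error

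*Protocol article*

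**What the plan says.** The abstract (Method/design) names two primary outcomes: "Primary outcomes are depressed mood and biochemically validated 7-day point prevalence abstinence from smoking over 12 months".

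Under Aim I, hypothesis 1a predicts "significantly greater improvements in mood and significantly higher rates of biochemically verified 7-day point prevalence abstinence over 12 months than control patients". The next sentence is "This trial is powered for hypothesis 1a analyses".

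The Power section opens with "The proposed study is fully powered for both Aim I primary outcomes" and then treats the outcomes one at a time:
- **Abstinence:** the calculation starts "Given the assumptions above and an alpha level of 0.05" and arrives at 324 participants for 80% power on a longitudinal odds ratio of 1.33.
- **PHQ-9:** the same 324 participants are said to give more than 80% power for small effects, with 80% quoted at f squared = 0.03. No expected PHQ-9 effect is given.

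Primary outcome analyses gives each outcome its own model. The article states no joint power, no division of alpha and no testing order, and does not say whether 1a needs one significant result or two.

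Table 1 lists "Depressive symptoms (CESD-10 [66" among the primary outcomes. The Mood and quality of life outcomes section calls the CESD-10 secondary, and Secondary outcome analyses handles it as such.

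**The concern.** A hypothesis that asserts significance on two outcomes is supported only when both tests succeed. The probability of that cannot exceed the lower of the two separate powers, and it falls below it unless the other test is almost certain to succeed or the tests are very strongly correlated. Two figures of about 80% therefore do not make the trial 80% powered for 1a as written.

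The alternative is to treat the outcomes as two claims, each able to stand alone. The stated power then describes each claim correctly, but there are two primary tests and abstinence has already been given the full 0.05. The chance of at least one false primary finding then exceeds 5%.

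A reader cannot tell from the article whether one significant outcome makes a positive trial. Either answer changes what the stated power or the stated alpha means, and the choice should not be open once the results are known.

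**Working it through.** **Inputs from the article.** N = 324; alpha 0.05, sidedness not stated; abstinence power 80%; PHQ-9 power 80% or more at f squared = 0.03.

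**Assumptions.** Two-sided tests; correlation between the two test statistics 0 to 0.5; no dropout.

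**1. The plan's own figures.**
- *PHQ-9:* noncentral F with λ = 0.03 × 324 = 9.72. With 2 numerator degrees of freedom the power is 80.0%, which matches the quoted 80%. With 1 degree of freedom (a single group effect) it is 87.5%, which fits the wording of more than 80%. Both values are carried forward.
- *Abstinence:* the 80% is taken at face value. It cannot be reproduced from the article, which omits the within-person correlation, the sidedness and the course of the rates over time. For example, odds ratio 1.33, control rate 29%, two-sided 0.05 and zero within-person correlation give 67% power at 324. That is a separate matter and nothing below relies on it.

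**2. Both required.** Joint power = Φ₂(z₁, z₂; ρ), where z₁ and z₂ are the normal quantiles of the two separate powers. At ρ = 0 this is their product, for example 0.80 × 0.80 = 0.64.

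| Abstinence / PHQ-9 power | ρ = 0 | ρ = 0.3 | ρ = 0.5 |
|---|---|---|---|
| 80% / 80% | 64.0% | 66.6% | 68.7% |
| 80% / 87.5% | 70.0% | 72.0% | 73.6% |
| 80% / 99% | 79.2% | 79.5% | 79.7% |

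To put the loss in terms of sample size: with equal powers and independence, 80% joint power needs √0.80 = 89.4% on each test. N scales as 324 × [(1.960 + 1.250) / (1.960 + 0.842)]² ≈ 426.

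**3. Either may stand alone, each at 0.05.** Chance of at least one false rejection when neither effect exists:
- independent: 1 − 0.95² = 9.75%
- correlation 0.5: 9.1%

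These count rejections in either direction. Counting only false findings in favour of BAT-CS, each test contributes 2.5% and the pair about 4.9% (1 − 0.975²), so the near-doubling is the same.

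**4. What Holm costs abstinence.** A test with 80% power at two-sided 0.05 has a standardised effect of 1.960 + 0.842 = 2.802. At 0.025 the critical value is 2.241, so power is Φ(2.802 − 2.241) = 71.2%. Under Holm, abstinence may be tested at 0.05 once PHQ-9 passes 0.025. With independent tests:
- PHQ-9 has no effect: 0.712 + (0.800 − 0.712) × 0.025 ≈ 71%
- PHQ-9 has 80% power: 0.712 + (0.800 − 0.712) × 0.712 ≈ 77%

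**The case against.** **The separate-claims reading.** The strongest reply is that the article promises neither joint power nor a family-wise 5%. Aim I speaks of analyses in the plural, the Power section gives one figure per outcome, and each outcome has its own model. Read as two claims reported separately, each has its stated power. This stands as far as it goes: it rescues the per-outcome power. It does not fit a single hypothesis that asserts both results, and it leaves two primary outcomes each tested at the full 0.05.

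**The unseen analysis plan.** A multiplicity rule may sit there, and its absence from an article is no fault. That is accepted. The point rests on what the article does state: a two-part hypothesis described as powered, and a calculation for each part alone with abstinence at full alpha.

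**The unknown PHQ-9 effect.** The value f squared = 0.03 is a detectable effect, not an expected one, so 64% is the low end of a range and not an estimate. This also stands, and the range has to be shown up to about 79%.

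**Stronger readings that the article does not support:**
- A reader might infer from the Discussion ("If this study shows BAT-CS to be efficacious for smoking, we plan to propose a multi-site effectiveness study") that success will be judged on smoking alone, or on either outcome. That sentence sets a condition for follow-on research and is not a success rule for this trial. Even if smoking alone decided, there would be one test, with 5% error and the stated 80% power.
- A reader might take Table 1 to make CESD-10 a third primary outcome and compute 1 − 0.95³ = 14.3%. The text calls CESD-10 secondary, and two depression scales in the same patients are unlikely to be independent.

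**Conclusion.** The point holds in a limited form: the stated power does not apply to hypothesis 1a as worded. If both outcomes must be significant, power is 64–74% on the article's own per-outcome figures with a correlation of 0 to 0.5. It reaches about 79% only if PHQ-9 power is about 99%, and it cannot exceed the 80% for abstinence. If each outcome may carry its own claim at an unadjusted 0.05, the chance of at least one false primary finding is 9.1–9.75%.

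It does not follow that the trial is badly underpowered, or that its error rate is certainly inflated. The first depends on a PHQ-9 effect that the article does not give, and the second on a decision rule that it does not fix. These results take the 80% for abstinence as stated and assume two-sided tests and no dropout. The Table 1 entry for CESD-10 is a labelling slip and has no bearing on the size of this problem.

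**What to change.** 1. In Aim I, state that 1a is supported only if abstinence and PHQ-9 are both significant at two-sided 0.05. This rule needs no alpha adjustment.
2. In Aim I and the Power section, describe the existing power as per-outcome and put the joint range beside it: 64–74%, approaching 79% if PHQ-9 power is about 99%.
3. If an efficacy claim on one primary outcome alone is to be allowed, use Holm: the smaller p-value against 0.025, the other against 0.05. The two rules differ when both p-values lie between 0.025 and 0.05, where 1a would be supported but Holm would allow no single claim. Record before unblinding which rule governs which claim.
4. As a separate minor correction, move CESD-10 to the secondary block of Table 1.

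**Cost.** Wording and a pre-specified testing rule, with no extra patients. The stated power becomes less favourable: the joint range for 1a, and for an abstinence claim under Holm about 71% if PHQ-9 shows no effect or about 77% if PHQ-9 has 80% power and the tests are independent.

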### Aim II

Test the efficacy of BAT-CS versus control on cardiac health. *Hypothesis 2a*: Patients treated with BAT-CS will have greater functional capacity and lower rates of major adverse cardiac events (i.e., hospitalization for unstable angina, urgent coronary revascularization, myocardial infarction) and all-cause mortality.

### Aim III

Explore hypothesized mediators of treatment effects (see Fig. 1). *Hypothesis 3a*: Between group differences in depressed mood will be mediated by changes in BA theory-based mechanisms (i.e., greater engagement in pleasant and personally valued activities). *Hypothesis 3b*: Between group differences in smoking cessation will be mediated by both changes in depressed mood and BA theory-based mechanisms.

**Fig. 1 Fig1:**
[figure not shown]
Conceptual model

### Aim IV

Explore the temporal interaction of smoking and multiple aspects of mood over 1-year post-ACS.

## Methods

### Study design overview

324 ACS patients who smoke will be recruited and randomly assigned to 12 weeks of either Behavioral Activation Treatment for Cardiac Smokers (BAT-CS; smoking cessation and BA based mood management counseling) or a control condition (smoking cessation and health education) that fully controls for BA contact time (see Fig. 2). All participants will be offered 8 weeks of the nicotine patch if medically appropriate. All counseling in both conditions will be provided by tobacco treatment specialists over 12 weeks post-discharge. Comprehensive assessments completed by blind to condition assessors will occur at end-of-treatment (12 weeks after discharge) and 6, 9, and 12 months after discharge. Major Adverse Cardiac Events (MACE; i.e., hospitalization for unstable angina, urgent coronary revascularization, myocardial infarction) and all-cause mortality will be tracked through the end of the study for up to 36 months (see Table 1 and Fig. 2). Recruitment began on 1/22/2018. This protocol is presented consistent with SPIRIT guidelines (see additional file 1).

**Fig. 2 Fig2:**
[figure not shown]
Design overview

**Table 1 Tab1:** Assessments by time point

	Screen	Baseline 1	Baseline 2	Each session	12 weeks/end-of-treatment	6, 9, 12 months	18, 24, 30, and 36 months
*Screening fully*							
Medical diagnosis, current smoking, and other inclusion/exclusion criteria	X						
Cognitive functioning (MMSE [43])	X						
*Participant characteristics*							
Demographics (age, race, etc.)		X					
Medical and smoking history		X					
Nicotine dependence (FTND [50])		X					
Motivation to quit (contemplation ladder [51])		X	X				
MN withdrawal scale [52]			X				
*Primary outcomes*							
Current smoking/smoking since last contact		X	X	X	X	X	X
Use of other tobacco products		X	X	X	X	X	X
Saliva sample for cotinine testing			X		X	X	
Exhaled breath sample for CO testing			X		X	X	
Depressive symptoms (PHQ-9 [53])		X	X		X	X	X
Depressive symptoms (CESD-10 [66])		X	X		X	X	
*Secondary outcomes*							
Positive and negative affect (PANAS [57])		X	X		X	X	X
Reactive anhedonia (SHAPS [68, 69])		X	X		X	X	
Perceived stress scale (PSS-4 [70])		X			X	X	
Health related quality of life (SF-12 [71])		X			X	X	
Exercise tolerance (DASI [72])		X			X	X	
MACE/mortality					X	X	X
Adverse event monitoring			X	X	X	X	X
*Hypothesized BA mediators*							
Pleasant/valued activities (BADS [76], PES [79, 80])		X			X	X	
*Acceptability*							
Treatment acceptability (CSQ-8 [81])					X		
*Potential confounders*							
Medication adherence questions [88, 89]		X			X	X	
Diet/exercise questions [92]		X			X	X	
Counseling sessions attended				X			
Cardiac rehabilitation attendance					X	X	
Outside of study depression treatment					X	X	
Outside of study smoking cessation treatment					X	X	

### Study setting

Recruitment will be conducted at several hospital sites in Minneapolis, MN and surrounding communities. Outcome assessment visits will be conducted at a hospital clinical outcomes center at the primary study site, in participant homes, by phone, or using secure video conferencing. MACE and mortality outcomes will be tracked via outcome assessments and medical records review.

### Participants

ACS is defined as a diagnosis of unstable angina, ST-elevation myocardial infarction, or non-ST-elevation myocardial infarction. ACS will be confirmed by coronary angiogram before enrollment. If diagnosis in the medical record was unclear or contradictory, a study cardiologist will review the case. Only Type I myocardial infarctions will be included (Type II myocardial infarctions caused by demand ischemia will be excluded). Myocardial infarction caused by spontaneous coronary artery dissection (SCAD) was included. We included SCAD cases because SCAD is associated with high rates of both smoking [39] and depression [40]. SCAD is also increasingly considered under the umbrella of ACS [41] and some have argued it should considered a cause of Type I myocardial infarctions [42]. Further, because SCAD occurs primally in women [41], including SCAD will improve gender balance in our study.

Individuals will be identified for recruitment while hospitalized on an inpatient unit for an ACS event. The hospitalization context can include both the initial emergency treatment for the ACS event, as well as subsequent hospitalizations within 30 days of the ACS event related to ACS treatment (e.g., returning to the hospital for bypass surgery). Additional inclusion criteria include (1) smoking ≥ 1 cigarette per day before hospitalization, (2) willing to consider quitting smoking at discharge, (3) age of 18–75, (4) English fluency, (5) lives within a 1.5 h drive from study site or willing to do all post-discharge study procedures remotely, (6) has regular access to a telephone or is willing and able to use a study issued cell phone, and (7) willing to consent to all study procedures. See Table 2 for a history of changes to inclusion criteria during the study.

**Table 2 Tab2:** Major protocol changes

Description	Date
Remuneration for counseling sessions 3–6 was added to protocol based on participant feedback that their participation was limited because phone calls were using up limited cell phone minutes	11/12/2018
Provision of study issued cell phones to participants without other telephone access was added to the protocol to increase recruitment	7/31/2019
Protocol was updated to allow for recruitment of patients hospitalized for ACS related treatment or complications within 30 days of an index ACS event. This change was made to increase recruitment, particularly of those who are discharged quickly following index ACS but have a planned return for revascularization treatment	9/24/2019
Participants living more than a 1.5 h drive away were allowed to participate if they were willing to do all post-discharge study procedures remotely, including bio-verification of smoking status via mail. This change was made to increase recruitment and because a device (i.e., the Bedfont iCO Smokerlyzer®) that allows for remote measurement of exhaled carbon monoxide had recently become available	9/24/2019
The protocol was updated to allow recruitment and consent up to 1-week post-discharge. This change was made due to COVID-19 related hospital inpatient unit access restrictions	5/4/2020
Procedures allowing for remote (i.e., without in person contact) written consent were added to the protocol. These changes allowed for the consent discussion via phone with signed documents mailed, scanned, or dropped off/picked up with no in person contact. This change was made due to COVID-19 related restrictions	5/4/2020
The original protocol hypothesized group differences in intermediate cardiac outcomes (i.e., blood pressure, HDL-cholesterol, fibrinogen, and high sensitivity C-reactive protein). These measures were originally collected via in person blood draws at outcome assessments. Due to COVID-19 restrictions on in person visits, collection of these outcomes was suspended on 3/17/2020. Collection of these outcomes was dropped permanently from the study protocol in 7/8/21 due to significant missing data and continued participant preference for remote visits due to COVID-19	3/17/2020 (collection suspended)
	7/8/21 (removed from protocol)
The protocol was updated to allow for digital signing of consent and HIPAA forms allowable (via REDCap). This change was made to streamline the remote consent process	8/7/2020
Secure Zoom video conferencing allowed for all contacts as needed	8/7/2020

Exclusion criteria will be (1) limited mental competency (i.e., Mini Mental Status Exam [43] score ≤ 20); (2) a current exacerbation of serious mental illness that would interfere with study participation or current suicidality; (3) expected discharge to hospice or > 50% chance of 6 month mortality per the Global Registry of Acute Coronary Events [44] (GRACE) risk calculator; and (4) currently attending counseling targeting depression or smoking cessation. Note that we did not require patients to have symptoms of depression at baseline because a significant percentage of ACS patients with depression experience symptom onset post-ACS [11, 45, 46]. We enrolled those smoking ≥ 1 cigarette per day based on ample evidence that even one cigarette a day has deleterious effects on cardiac health [47].

